### Study design

This study is randomized, double-blind clinical trial research that will be conducted on 40 women with experience of sexual assault referred to Iran-Isfahan Welfare and Forensic Medicine Centers. In the first phase of the educational intervention, the program, content and questionnaire will be designed and compiled, and in the second phase, sampling will be performed in the form of a census and, then, training sessions will be held. For the purpose of randomization, table of random numbers will be used for two intervention and control groups with a ratio of 1:1. The design of this clinical trial follows the requirements of the CONSORT statement.

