#### Second phase: implementation of the intervention and training sessions

The instructor is a Master of Forensic Midwifery student and all training is delivered under the supervision and approval of the research team and the research team's clinical psychologist, and the content is approved by the research team. Participants in the intervention group will be taught about health, hygiene, psychology and stress reduction methods in group or individual sessions according to their preference in 6 sessions of 60 min each, one session per week. After obtaining the ethics permission from Isfahan University of Medical Sciences and the IRCT code, a letter of introduction is obtained to be submitted to Isfahan Welfare and Forensic Medicine Organizations. Written permission will be obtained from the officials to enter and access the medical files, and the researcher will be present in the research environment and introduced to the officials. The objectives of the research and the method of doing the study will be explained. An educational intervention is designed and developed, taking into account the constructs of social cognitive theory and focusing on health-related behavior. Sampling will take the form of a census of the participants who meet the eligibility criteria after accessing the file in the above-mentioned centers, and they will be invited to participate in the study by telephone. The participants are randomly assigned to the intervention and control groups using a random number table. Before participating in the research, they will be given a description of the research objectives, the intervention method and sufficient assurances of confidentiality, and they will be able to choose whether to participate in group or individual sessions to receive the educational intervention. Written consent will be obtained from the participants to participate in the research, and pre-test will be performed. Participants allocated to the intervention group will be invited to participate in four groups of 5 participants according to their age and education, or if they do not wish to be in a group, they will be invited to attend individual sessions. Then, an educational intervention based on social cognitive theory will be implemented in the Welfare and Forensic Medicine Organizations during 6 sessions of 45–60 min once a week and for 6 weeks by a trained instructor. The qualification of this instructor is confirmed by the consulting professor, [name], [PhD in clinical psychology] during a three-session program with health-related educational content. In order to provide the educational intervention [attached], the student will conduct the intervention based on social cognitive theory constructs in sessions under the supervision and approval of the team psychologist, and two sessions will be carried out in the presence of the professor. The educational content has been prepared on the basis of theoretical constructs and using the scientific techniques available in psychological articles and books, and taking into account the conditions required for the training, and will be analyzed and approved by the supervisor and advisor. In order to make the intervention in the direction of social support and environment, according to the specific social conditions, educational brochures will be given to the individuals to have the influence of the environment, so that they can request social support from the supportive people or give the brochure to their supporters and receive the education indirectly. It should be noted that in parallel with the intervention group, in order to double-blind the control group, a one-hour session for the control group will be provided with the routine training of the above-mentioned centers, without focusing on specific theoretical structures and continuous follow-up of sexually transmitted diseases. During the study, they will use the services and routine care provided by the centers, they will not be deprived of these services, and the researcher will not know about the groups. The time required for the research process [proposal preparation and approval, sampling and intervention, final report and article preparation, article editing and submission] is 14 months. Brochures, booklets and CDs with the same content as the sessions are used as teaching methods to make the sessions more accessible. For two months after the end of the intervention, the participants will be followed up, if necessary, through a telephone line, virtual group and SMS, and their questions will be answered. A post-test will be conducted for both groups to check the effect of the educational intervention two months after the last intervention session in the intervention group. This study is conducted to measure the effect of the independent variable (intervention training) on the dependent variables health-related awareness, health-related attitude and behavior, self-efficacy, perceived social support and PTSD severity score of women with experience of sexual assault. It also aims to reduce the symptoms of stress disorder, increase awareness, and improve health-related attitude and behavior, self-efficacy and perceived social support. The variables of background characteristics, self-efficacy, perceived social support, post-traumatic stress disorder, awareness and health-related attitudes and behaviors will be measured using a self-report questionnaire before and two months after the intervention in two groups. The measurement tools used in this research include a questionnaire on demographic characteristics, a standard questionnaire on self-efficacy, a standard questionnaire on perceived social support, PCL-5 post-traumatic stress disorder questionnaire, and a researcher-made questionnaire on health-related awareness, attitude and behavior. The questionnaire will be filled as self-report, and if a participant is illiterate, it is read out to them. It is hoped that by using the constructs of social cognitive theory in the content of training sessions based on scientific documents, it will be possible to meet the needs of these participants and prevent further injury and problems.

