### Sample size

According to the mean values and standard deviation before and after the educational intervention in previous studies [26] and asking the opinions of statistics experts and considering α = 0.05 and β = 0.2, the standard deviations of 7.95 and 8.06 in the intervention and control groups, and a minimum difference of 7.5 points between the two groups in terms of post-traumatic stress disorder, the sample size is calculated to be 18 participants in each group. However, considering a drop-out rate of 10%, the sample size is set at 20 participants in each group.

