### Analysis

All statistical trials and confidence intervals will be supposed with a type I error established in alpha = 0.05, using the IBM SPSS V26 statistics package. The data in this research are of a quantitative and qualitative nature, and descriptive and inferential statistical methods are used for analysis. In order to achieve the research question, determine and compare the demographic characteristics (field) between the two test and control groups, from descriptive statistics tests, independent t-test for quantitative variables such as age and number of family members, for nominal qualitative variables such as occupation. Chi-square test was used and Mann–Whitney test was used for the qualitative variable, level of education, type of residence, child's birth rate. In order to achieve the objectives of the research, the analysis of variance with repeated measures will be used to investigate the main and combined effects, and then the Bonferroni post hoc test will be used to answer the objectives (comparison within each group) and objectives (comparison between two groups).

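### The repeated-measures ANOVA uses only women with both tests and does not adjust for pre-test PCL-5, so loss related to severity could bias the PTSD comparison in a direction that depends on who is lost

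*Protocol article*

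**What the plan says.** The Analysis section of the protocol article fixes one method for the study objectives: "the analysis of variance with repeated measures will be used to investigate the main and combined effects". It is to be run in SPSS V26 and followed by Bonferroni comparisons within each group and between the groups. The questionnaires are given twice, before the intervention and two months after it. The article does not say which of these effects decides the PTSD question.

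The Sample size section states that "the sample size is calculated to be 18 participants in each group" and then, "considering a drop-out rate of 10%, the sample size is set at 20 participants in each group". This is a single rate. It is not split by arm, and no reason for loss is given.

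Under the second phase of the intervention, the intervention arm attends six weekly sessions, whereas for controls "a one-hour session for the control group will be provided". The Control group section also mentions continuing training on follow-up of infections, but gives no number of sessions.

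**The concern.** With two measurement times, the group-by-time test in repeated-measures ANOVA is a comparison of mean change, and the between-group comparison at the second time is a comparison of post-test means. Both need both scores from each woman, and neither adjusts one score for the other.

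This matters little while randomisation keeps the arms comparable. It matters once the women who remain differ between arms at baseline. The arms ask for different amounts of attendance, and the Introduction itself describes PTSD as an obstacle to follow-up, so uneven, severity-related loss is plausible. The estimated PTSD effect would then depend on which planned comparison is read, and the article does not say which one that is.

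**Working it through.** **The plan's own figure.** Inputs from the Sample size section: "considering α = 0.05 and β = 0.2", "the standard deviations of 7.95 and 8.06 in the intervention and control groups", "a minimum difference of 7.5 points between the two groups in terms of post-traumatic stress disorder". Allocation is 1:1 (Study design). Taking the test as two-sided:

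n = (1.960 + 0.842)² × (7.95² + 8.06²) / 7.5² = 7.849 × 128.17 / 56.25 = 17.88, rounded up to 18. Then 18 / 0.90 = 20. Both stated figures reproduce.

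**Power is not the issue.** Normal-approximation power is 80.3% with 18 and 18 analysed, and 79.8% with 16 and 20. Uneven loss costs almost nothing in power, so the question is bias.

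**Assumptions not in the documents.** Pre-post correlation ρ is 0.5, with a range of 0.3 to 0.7. The split of the 4 expected losses (10% of 40) is taken as 20%/0%, 15%/5% or 10%/10%, intervention/control. The reason for loss is varied. Negative values favour the intervention.

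**Extreme case: exactly the most severe women at baseline leave the intervention arm only.** With SD 8 and loss fraction q, the completers' baseline mean falls by 8 × φ(z) / (1 − q), where z is the upper-q normal quantile.

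- q = 0.10: 8 × 0.1755 / 0.90 = 1.56
- q = 0.20: 8 × 0.2800 / 0.80 = 2.80

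The bias is −ρ × shift in the post-test difference and +(1 − ρ) × shift in the change difference. At ρ = 0.5 these are −0.78 and +0.78 for q = 0.10, and −1.40 and +1.40 for q = 0.20. At q = 0.20 they are −0.84 and +1.96 for ρ = 0.3, and −1.96 and +0.84 for ρ = 0.7.

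**Graded loss.** Simulation with 400,000 women per arm, no true effect, and log-odds of loss rising by 1 per SD of the driver. Loss 20%/0%, ρ = 0.5:

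| Loss depends on | Post-test difference | Change difference | Likelihood model using all pre-tests |
|---|---|---|---|
| High baseline | −0.71 | +0.68 | −0.02 |
| High post-test | −1.38 | −0.71 | −1.07 |
| Poor change | −0.70 | −1.40 | −1.07 |
| Nothing (random) | −0.01 | 0.00 | −0.01 |

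At 15%/5% the biases roughly halve. At 10%/10% with the same mechanism in both arms they are about 0. The pattern of signs holds for ρ from 0.3 to 0.7. For baseline-driven loss at 20%/0%, the post-test bias runs from −0.44 to −0.94 and the change bias from +0.98 to +0.43.

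**What removes the baseline-driven bias.** Selection on the pre-test leaves the regression of post-test on pre-test unchanged, so any analysis that conditions on the pre-test is protected. In simulations of the extreme case with a true effect of −7.5 (20 per arm, ρ = 0.5), the unadjusted comparisons gave −8.24 (post-test) and −6.75 (change) at 10% loss, and −8.75 and −6.19 at 20%. ANCOVA on completers alone gave −7.48 and −7.50. The cause in this scenario is therefore the lack of adjustment, not the discarding of lost women's pre-tests.

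**Precision.** In units of the post-test variance, the variance factor is 1 for the post-test difference, 2(1 − ρ) = 1 for change at ρ = 0.5, and 1 − ρ² = 0.75 for the adjusted analysis. The standard error falls to √0.75 = 0.87 of its unadjusted value.

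**The case against.** A reader might infer that uneven loss by itself biases the PTSD tests, and always in opposite directions. The documents do not support that. Random uneven loss gives no bias, and opposite signs need loss that depends on baseline PCL-5. The article gives neither a mechanism nor a split by arm. The reading closest to its own allowance, 18 becoming 20 in each group, is equal loss, for which the bias is about 0 if the mechanism is also alike.

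A reader might also take 1.4 points as the expected size. It is an extreme, with perfect truncation and every loss in one arm. Graded loss gives about half. The sampling standard deviation of either estimate is about 8 × √(1/18 + 1/20) = 2.6 points, so 0.7 is roughly a quarter of a standard error.

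It can be added that the 10% may include women removed under the exclusion criteria for missed sessions or a new crisis, since the article does not say, and that missing-data rules usually sit in an analysis plan not shown here. Both points are fair, and the absence of such rules is not criticised. What stands is that the article names a method, and that method neither adjusts for the pre-test nor uses a woman without a post-test. A missing-data section elsewhere would have to replace or supplement it.

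**Conclusion.** The concern holds in conditional form. The named ANOVA leaves the PCL-5 comparison open to bias if loss is related to severity and differs between arms. If the driver is baseline severity, the post-test and change comparisons err in opposite directions: about 0.7 points each under graded loss (9% of the 7.5-point target), and about 1.4 (19%) if exactly the worst 20% of the intervention arm leave. Both figures assume ρ = 0.5 and all four expected losses in that arm. If the driver is the post-test score or poor change, both comparisons err the same way, towards the intervention when poor responders leave that arm. The direction in this trial cannot be asserted. The plan should be changed because a better analysis uses data already being collected, but the flaw does not invalidate the trial.

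**What to change.** For PCL-5, name one baseline-conditioned analysis of the post-test as the deciding one. One option is a linear mixed model (SPSS MIXED) on all randomised women, with pre-test and post-test as responses, a common pre-test mean, an unstructured covariance and an arm effect at the post-test. The other is ANCOVA of the post-test on the pre-test, which gives essentially the same protection here. Either removes bias from baseline-dependent loss and improves precision.

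Seek the post-test from every randomised woman whatever her attendance. The model only partly corrects loss driven by the unseen post-test: at 20%/0%, a bias of about −1.4 falls to −1.28 at ρ = 0.3 and to −0.76 at ρ = 0.7. Under loss driven by poor change at ρ = 0.5 it leaves −1.07, which lies between the two unadjusted comparisons.

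For the same reason, add a sensitivity analysis that worsens missing intervention-arm post-tests by 0 to 7.5 points. With 4 of 20 missing, the largest shift moves that arm's mean by 4/20 × 7.5 = 1.5 points.

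The cost is revised wording, slightly more analysis work and some effort in obtaining post-tests. No extra women or visits are needed, and Trial status reports that 40 have already been selected. The downside is that the main analysis relies on loss being explained by the pre-test, which the sensitivity analysis probes.

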## Discussion

Sexual assault has many effects on mental and physical health and is linked to various personal, social and environmental issues. Besides physical complications, sexual assault causes psychological and social damage. Since the complications caused by sexual assault include the damage to a girl's virginity, it can lead to psychosocial complications in traditional societies and add to its psychological complications. These complications, as gender-related complications, can in turn affect a person's sexual identity. The social consequences of sexual assault are a serious problem for the female survivors in traditional societies, as they are often reluctant to disclose the incident and therefore do not receive social support from their families. Accordingly, this poses a serious challenge to their access to reproductive and mental health services. The possibility of pregnancy is another serious problem for these women, and the lack of access to legal abortion can lead these women to the process of illegal abortion and its complications. The lack of awareness of health rights and legal and civil protection and their negative attitude towards seeking health services due to the fear of disclosing rape, together with the reduction in receiving and seeking social support among these women and their families, can explain the possibility of the effectiveness of the program based on social cognitive theory. It is expected that prevention strategies, resources and early treatment, as well as strategies for rehabilitation, education and awareness of reproductive and sexual health, will be provided in order to prevent the health-related disruption rape can cause and its negative consequences [36, 37]. Because rape causes physical, mental and emotional damage, many countries have taken various measures to change the law and increase support for sexual assault survivors, including the establishment of rape crisis clinics. However, in our country, in addition to the weaknesses in the laws relating to sexual assault and how to prove it, no measures have been taken regarding support and compensation for emotional and psychological damage, and in many cases, victims receive no support and are unable to return to their normal lives [38]. Affected by gender stereotypes and the culture of patriarchal societies, women are considered to be the weak and second sex, and their position has been weakened. Efforts to eliminate stereotypes and raise awareness can help to purge societies of sexual violence [39]. Lack of attention to the psychological needs and treatment of individuals who have experienced sexual assault can lead to them becoming secondary victims and [40]. The essence of humanity is the ability to exercise control over life and to have personal, environmental and social agency to control one's personal destiny and social life. Social cognitive theory is an important theory that considers all three dimensions of person, environment and society [41]. Based on this theory, people can help to improve their life and create social changes [42]. Social cognitive theory focuses on how patterns of behavior are learned and how they function in interaction between the individual and the environment. Thus, not only does the individual's response to the environment play a central role, but intellectual processes, i.e., cognitive operations resulting from human interaction with the environment, and intrapersonal factors also play a fundamental role [43]. Social cognitive theory examines various structures of awareness, outcome expectations, situational awareness, environment, self-efficacy, self-efficacy in overcoming obstacles, self-control or goal setting, and emotional coping [44, 45]. It seems that the use of this theory in designing the content of educational interventions can be useful and practical.

## Conclusion

This study provides important information about the clinical effectiveness of educational interventions as part of PTSD treatment. It is expected that the present study will show that educational intervention is relatively inexpensive and can help support individuals.

### Trial status

This research was registered in Iran Clinical Trials Registration IRCT20230926059526N1 on 26 October 2023. To date, 40 participants have been randomly selected. It is expected that the recruitment of participants will be completed in March 2024.

## Data Availability

No datasets were generated or analysed during the current study.

## Abbreviations

PTSD: Post traumatic stress disorder
SCT: Social cognitive theory
